### Statistical analysis

#### Sample size

Power analyses are based on the results from the pilot study.^22^ For the biomarker panel, specificity was 91% at a sensitivity of 88%; however, power analysis was based on individual biomarkers to have an adequate sample size for assessment of both the individual markers and the panel. For individual biomarkers, sensitivity ranged from 76% to 87%, and specificity ranged from 72% to 95%. Lower bounds were used for the calculations, to ensure an adequate sample size. To assess specificity, with an α of 0.05, with (1 − α) % confidence level and a maximum marginal error of estimate of 0.10 (δ) for constructing CI of true value of specificity, assuming a value of 72% and using the normal approximation, and a disease prevalence of 30%, the total N needs to be 110. For sensitivity, using an assumption of sensitivity 76%, N would be 234.^27^ With an estimated drop-out of 5%, 246 patients need to be included.

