#### Analysis of outcome measures

All statistical analyses will be performed using IBM SPSS V.29. Baseline characteristics will be summarised by standard descriptive statistics.

Areas under the receiver operating characteristics (ROC) curves for identifying UTI will be calculated to assess the diagnostic power of the individual biomarkers. For each biomarker, the optimal cut-off will be determined based on the ROC curves, and the associated sensitivity and specificity, positive and negative predictive values, and positive and negative likelihood ratios will be reported. An additional logistic regression analysis will be performed to assess the value of combination(s) of biomarkers, aiming at a minimal sensitivity and specificity of 80%. For urine leukocytes, the above-mentioned parameters will be reported for a cut-off of 200 leukocytes/µL.

Subgroup analyses will be performed to assess the performance of biomarkers in males and females, different settings (hospital, primary care setting and long-term care) and different clinical presentations (systemic symptoms vs localised symptoms). Categorical values will be compared using the Fisher exact test or Pearson χ2 test.

Additional comparative analyses will be performed to compare biomarker levels in UTI with and without systemic symptoms. To assess the correlation between biomarker levels and time to resolution of symptoms and length of hospital stay, Pearson’s correlation coefficient will be used. For the calculation of the association between biomarker levels and complications of UTI and recurrence of UTI, logistic regression will be used.

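### The ±0.10 margin holds only for a cut-off fixed in advance, so it is not assured for the biomarkers, whose cut-offs are taken from the study's own ROC curves

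*Protocol article*

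**What the plan says.** The Sample size section says that the calculation rests on the individual biomarkers, so that N is adequate for both the single markers and the panel. Planning values are the lower ends of the pilot ranges. The calculation works at 95% confidence with a normal approximation, and its target is "a maximum marginal error of estimate of 0.10 (δ) for constructing CI of true value of specificity, assuming a value of 72" per cent. At 30% prevalence this comes to 110 patients in all. The step that sets N reads: "For sensitivity, using an assumption of sensitivity 76%, N would be 234". A 5% drop-out allowance gives 246.

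The section Analysis of outcome measures then sets out how biomarker accuracy is obtained: "For each biomarker, the optimal cut-off will be determined based on the ROC curves, and the associated sensitivity and specificity" are reported, together with predictive values and likelihood ratios. No biomarker cut-off is given in advance and the meaning of optimal is not stated. Pyuria is different: its accuracy is reported at 200 leukocytes/µL, a value carried over from the pilot study.

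**The concern.** The one-proportion formula treats the number of cases above the cut-off, and of non-cases below it, as binomial. That is right if the cut-off was set before the data were seen. If it is picked from the ROC curve of the same patients, two things change. The chosen point moves along the curve from sample to sample, so sensitivity and specificity trade off against each other. The point is also picked because it looks good in this sample, so the apparent accuracy is too high on average.

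The formula thus fits pyuria, on which N was not based, and does not fit the individual biomarkers, on which it was. The ±0.10 margin at 95% confidence is the only precision argument for 246 patients. The study's aim is to validate these markers and to select one or more for a point-of-care test. Readers who take ±0.10 at face value, or see ordinary binomial intervals at the chosen cut-offs, would think a marker's accuracy better established than it is.

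**Working it through.** **Inputs.** From the Sample size section: 95% confidence (z = 1.96), δ = 0.10, specificity 0.72, sensitivity 0.76, prevalence 0.30, drop-out 5%. Cases in 234 patients: 0.30 × 234 = 70.2, so about 70 cases and 164 non-cases.

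**The plan's own figures.** The formula is n = z²p(1−p)/δ², divided by the share of patients who contribute.

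- Specificity: 1.96² × 0.72 × 0.28 / 0.01 = 77.4 non-cases; 77.4 / 0.70 = 110.6 (stated 110).
- Sensitivity: 1.96² × 0.76 × 0.24 / 0.01 = 70.07 cases; 70.07 / 0.30 = 233.6 (stated 234).
- Drop-out: 234 × 1.05 = 245.7, or 234 / 0.95 = 246.3 (stated 246).

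The figures reproduce up to rounding.

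**Fixed cut-off at N=234.** Half-width for sensitivity 1.96 × √(0.76 × 0.24 / 70.2) = 0.100; for specificity 1.96 × √(0.72 × 0.28 / 163.8) = 0.069. For pyuria at the pilot's 89% and 86%: 1.96 × √(0.89 × 0.11 / 70) = 0.073 and 1.96 × √(0.86 × 0.14 / 164) = 0.053. With a cut-off fixed in advance, the design meets its margin.

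**Cut-off chosen from the data.** This needs assumptions that the article does not supply: a marker distribution and a rule for optimal. Studies of 70 cases and 164 non-cases were simulated (4,000 to 20,000 per scenario). The marker was equal-variance binormal with separation Φ⁻¹(0.76) + Φ⁻¹(0.72), giving an AUC of about 0.82 and a true optimum of 74%/74%. The cut-off was chosen afresh in each study.

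*Target A: accuracy at the true optimal cut-off.* Half-width = 1.96 × SD of the estimate.

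| Rule | Sensitivity | Specificity |
|---|---|---|
| Maximum sensitivity + specificity | about 0.16 | about 0.16 |
| Maximum product | 0.130 | 0.123 |
| Closest to (0,1) | about 0.10 | about 0.10 |
| Sensitivity = specificity | 0.061 | 0.062 |

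With case-to-control SD ratios from 0.8 to 1.5, the maximum-sum rule gives 0.150-0.164 for sensitivity and 0.134-0.161 for specificity. Closest-to-(0,1) gives 0.099-0.101 and 0.093-0.098.

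Stronger markers under the maximum-sum rule have smaller sensitivity half-widths: about 0.13 at 80%/80%, 0.09 at 87%/87%, 0.087 at 76%/95% and 0.068 at 87%/95%. At 87%/72% it is still 0.128.

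*Target B: true accuracy at the cut-off actually chosen.*

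| Rule | Bias, sens. / spec. | 1.96 SD of error, sens. / spec. | Binomial 95% coverage, sens. / spec. |
|---|---|---|---|
| Maximum sum | +0.040 / +0.013 | 0.094 / 0.063 | 85% / 93% |
| Closest to (0,1) | +0.030 / +0.009 | 0.099 / 0.065 | 89% / 94% |

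Maximum product lies in the same range for sensitivity (bias +0.03 to +0.04, coverage 85-90%). Under sensitivity = specificity the bias is negligible.

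**The case against.** Four objections deserve an answer.

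**The size depends on an unstated rule.** This stands. A reader might infer that ±0.10 is plainly missed and that the true margin is ±0.15 to ±0.16. That needs the maximum-sum rule, which the article does not state. Closest-to-(0,1) gives about ±0.10, and one rule gives about ±0.06. For the same reason, the N of roughly 1,100 to 1,300 that the maximum-sum rule would need for ±0.10 is no argument for a larger study.

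**Extra variance is not the issue if the target is accuracy at the chosen cut-off.** This also stands. The article reports the accuracy that goes with the chosen cut-off, so target B is the more natural one. There the spread of the error (0.094 and 0.063 under maximum sum) is no larger than the fixed-cut-off 0.100 and 0.069. A reader might infer that a variance shortfall would persist after correcting for optimism; on this target it would not. What remains is the optimism itself and the under-coverage that it causes.

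**The planning values are a worst case.** In part. The 76% and 72% are minima of separate ranges and may belong to different markers; markers with specificity near 95% stay inside ±0.10 under the maximum-sum rule. But the section uses the minima precisely so that N is adequate for the weakest marker, and there the margin is least assured.

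**Interval methods belong in an analysis plan.** True of the interval method, and the article does not say that it will use binomial intervals. The point does not rest on that omission. The article itself states both a precision claim that needs a fixed cut-off and a cut-off rule that does not provide one.

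**Conclusion.** The point holds in limited form. The margin of ±0.10 at 95% confidence is justified for pyuria at 200/µL, the only primary outcome with a stated cut-off fixed in advance. It is not assured for the individual biomarkers, on which N is based. There is no arithmetic error, and N does not have to change.

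The size rests on a binormal marker at 76%/72% with 70 cases and 164 non-cases, and on the unnamed criterion. Around accuracy at the true optimum, the 95% half-width is about ±0.06 to ±0.16. Against true accuracy at the chosen cut-off, apparent sensitivity is about 0.03 to 0.04 too high and binomial intervals cover about 85-90% under the maximum-sum, maximum-product and closest-to-(0,1) rules.

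**What to change.** Keep N=246.

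- **Sample size.** State that ±0.10 applies to a cut-off fixed in advance and is not assured for ROC-derived cut-offs. Give the range of about ±0.06 to ±0.16 at the planning values, with its assumptions.
- **Analysis of outcome measures, cut-off.** Name the criterion for the optimal cut-off. Alternatively, use the pilot study's biomarker cut-offs, if available, for the primary accuracy estimates; the fixed-cut-off formula would then apply.
- **Analysis of outcome measures, estimates.** For ROC-derived cut-offs, report optimism-corrected sensitivity, specificity, predictive values and likelihood ratios, with bootstrap intervals that repeat the cut-off selection in every resample.

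The cost is a few sentences and a short script, possibly outside SPSS, with no extra patients or measurements. The downside is a less favourable stated margin, somewhat lower biomarker estimates and wider intervals.

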#### Analysis of outcome measures

All statistical analyses will be performed using IBM SPSS V.29. Baseline characteristics will be summarised by standard descriptive statistics.

Areas under the receiver operating characteristics (ROC) curves for identifying UTI will be calculated to assess the diagnostic power of the individual biomarkers. For each biomarker, the optimal cut-off will be determined based on the ROC curves, and the associated sensitivity and specificity, positive and negative predictive values, and positive and negative likelihood ratios will be reported. An additional logistic regression analysis will be performed to assess the value of combination(s) of biomarkers, aiming at a minimal sensitivity and specificity of 80%. For urine leukocytes, the above-mentioned parameters will be reported for a cut-off of 200 leukocytes/µL.

Subgroup analyses will be performed to assess the performance of biomarkers in males and females, different settings (hospital, primary care setting and long-term care) and different clinical presentations (systemic symptoms vs localised symptoms). Categorical values will be compared using the Fisher exact test or Pearson χ2 test.

Additional comparative analyses will be performed to compare biomarker levels in UTI with and without systemic symptoms. To assess the correlation between biomarker levels and time to resolution of symptoms and length of hospital stay, Pearson’s correlation coefficient will be used. For the calculation of the association between biomarker levels and complications of UTI and recurrence of UTI, logistic regression will be used.

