It is therefore crucial to improve diagnostic accuracy for UTI in older adults, particularly those with comorbidities and frailty.^7 18 19^ By providing reliable diagnostic markers together with appropriate cut-off values for UTIs in this population, suboptimal or delayed treatment can be avoided, which would significantly impact disease burden and improve patient outcomes. Multiple studies have identified useful biomarkers for the diagnosis of UTI.^20 21^ A recent study conducted by our group in a well-defined cohort of older women identified five promising markers for the diagnosis of UTIs. These include neutrophil gelatinase-associated lipocalin (NGAL), interleukin 6 (IL-6), azurocidin (AZU), tissue inhibitor of metalloproteinase 2 (TIMP2) and CXC motif chemokine ligand 9 (CXCL-9).^22^ NGAL is a protein that is produced by neutrophils and epithelial cells in the urinary tract and is a marker of injury and inflammation. IL-6 is a pro-inflammatory cytokine. AZU, a heparin-binding protein, is also released by neutrophils and has been identified as a marker of sepsis. TIMP-2 is a regulator of matrix metalloproteinases. CXCL9 is a chemokine induced by interferon gamma that is involved in the recruitment and activation of T cells and natural killer cells. These biomarkers hold significant potential for a new diagnostic test. In addition to these novel biomarkers, in the same cohort, the performance of an existing diagnostic tool: the urinary leucocyte (pyuria) count was investigated. The study showed that current cut-off values for pyuria lack specificity in older patients and proposed a higher, age-specific cut-off for the diagnosis of UTI. This age-specific cut-off could improve the performance of currently available diagnostic tests by tailoring their interpretation to the specific needs of older patients.

The UTI-GOLD study aims to validate five new biomarkers and the higher cut-off value for pyuria for UTI diagnosis in older patients in different real-world healthcare settings.

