### Outcome measures

The primary outcomes of this study are the diagnostic accuracy of the individual urine biomarkers (NGAL, IL-6, AZU, TIMP 2, CXCL9), a combination of biomarkers and the pyuria cut-off level of 200 leukocytes/µL. This cut-off level is based on the results of the pilot study which showed that 200 leukocytes/µL resulted in specificity of 86% while maintaining a high sensitivity of 89%.^16^ For the definition of a UTI, a recently developed international reference standard will be used, whereby patients will be categorised as having a definite UTI, probable UTI, possible UTI or no UTI.^26^ This reference standard was developed in a worldwide Delphi procedure and consists of (1) local signs/symptoms including LUTS, (2) systemic signs and symptoms, (3) routine urinalysis results and (4) culture results. In this manner, a more accurate and standardised approach is used to minimise misclassification. To investigate the relationship between biomarker levels and disease severity and recurrence, the following secondary outcomes are chosen: the duration of symptoms in days, complications including bacteremia, sepsis, septic shock defined in accordance with the quick sequential organ failure assessment score, and renal or prostatic abscess confirmed by ultrasound or CT scan, lengths of hospital stay in days and the frequency of recurrence of UTI defined by international reference standard within 2 months after inclusion.

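### Biomarker cut-offs and the combined panel are derived and evaluated on the same patients, so their reported accuracy is optimistic and no biomarker cut-off is validated

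*Protocol article*

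**What the plan says.** The Introduction gives the purpose: "The UTI-GOLD study aims to validate five new biomarkers and the higher cut-off value for pyuria for UTI diagnosis". Under Outcome measures, the primary outcomes are the accuracy of the five individual biomarkers, of a combination of them, and of the pyuria cut-off.

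The section Analysis of outcome measures then treats these tests in different ways:

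- **Single biomarkers, no threshold:** "Areas under the receiver operating characteristics (ROC) curves for identifying UTI will be calculated to assess the diagnostic power of the individual biomarkers".
- **Single biomarkers at a threshold:** "For each biomarker, the optimal cut-off will be determined based on the ROC curves, and the associated sensitivity and specificity", with predictive values and likelihood ratios. The criterion that makes a cut-off optimal is not defined.
- **Combination:** a logistic regression on the study data to "assess the value of combination(s) of biomarkers, aiming at a minimal sensitivity and specificity of 80" per cent.
- **Pyuria:** "For urine leukocytes, the above-mentioned parameters will be reported for a cut-off of 200 leukocytes/µL". Outcome measures explains the source of this value: "This cut-off level is based on the results of the pilot study".

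The Sample size section quotes pilot accuracy for each marker: "For individual biomarkers, sensitivity ranged from 76% to 87%, and specificity ranged from 72% to 95" per cent. A sensitivity and specificity presuppose a cut-off, so the pilot must have used some. The article gives none of their values and carries none forward.

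**The concern.** If a threshold is picked because it performs best in a set of patients, its accuracy in those patients is too favourable on average, because the search also exploits chance features of the sample. That is derivation. Validation means fixing the rule first and then seeing how it performs in new patients. The plan does this for pyuria but not for the five biomarkers or their combination.

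This is more than a detail left to an analysis plan. The article states the rule, and the rule as stated produces the bias. It matters because Future implications says the results will be used to choose the biomarker signature for a point-of-care test. Such a test needs a threshold that works in patients who played no part in choosing it. The 80%/80% target makes the panel especially exposed, since it can look met when it is not.

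**Working it through.** **1. The plan's own sample size.** Inputs from the Sample size section: half-width 0.10, 95% confidence, sensitivity 0.76, specificity 0.72, prevalence 0.30, drop-out 5%. Formula: n = 1.96² × p(1 − p) / 0.10².

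- Specificity: 3.8416 × 0.72 × 0.28 / 0.01 = 77.4 without UTI; 77.4 / 0.70 = 110.6 in total (plan: 110).
- Sensitivity: 3.8416 × 0.76 × 0.24 / 0.01 = 70.07 with UTI; 70.07 / 0.30 = 233.6, so 234 (plan: 234).
- Drop-out: 234 × 1.05 = 245.7, so 246 (plan: 246).

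The figures reproduce. The formula treats the cut-off as fixed beforehand. The analysed cohort is 0.30 × 234 ≈ 70 with UTI and 164 without.

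**2. Simulation of the stated cut-off rule.** Assumptions, because the article does not settle them: a marker that is normal with equal variance in both groups, and optimal meaning the maximum Youden index (sensitivity + specificity − 1). The separation between groups is z(sensitivity) + z(specificity), so that the ROC curve passes through the pilot pair. For 76%/72% this is z(0.76) + z(0.72) = 1.289, an AUC of 0.819. In each of 10,000 simulated studies, the cut-off was searched over all observed values, and the apparent accuracy was compared with the true accuracy of that same cut-off. The corners of the pilot range give (differences taken before rounding):

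| Pilot pair (sens/spec) | Apparent sens/spec | True sens/spec at chosen cut-off | Optimism, points |
|---|---|---|---|
| 76/72 | 76.8/75.4 | 72.8/74.0 | +4.0/+1.4 |
| 87/72 | 82.7/81.5 | 79.1/80.4 | +3.5/+1.1 |
| 76/95 | 89.9/88.9 | 87.0/88.0 | +2.9/+0.9 |
| 87/95 | 93.3/92.5 | 90.7/91.8 | +2.6/+0.7 |

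Repeat runs agree to about 0.1 point. Sensitivity suffers more because the UTI group is smaller. With a cut-off fixed in advance, the bias is at most 0.1 point in every row. The mean AUC in the first row is 0.820 against a true 0.819, so the AUC is not affected.

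The likelihood ratios inherit the bias. From the first row's averages, LR+ is 0.768 / 0.246 = 3.1 apparent against 0.728 / 0.260 = 2.8 true. LR− is 0.232 / 0.754 = 0.31 against 0.272 / 0.740 = 0.37.

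**3. Interval coverage.** The article names no interval method for the results. Across the four corners, a nominal 95% interval for the sensitivity of the chosen cut-off covers about 91–94% of the time with Wilson limits and about 78–85% with Wald limits.

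**4. The combination.** Illustration: five markers, each with the 76%/72% curve, assumed equal correlation, logistic regression on all five, Youden cut-off, 70/164 patients, 1,500 runs.

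| Assumed correlation | Optimism sens/spec, points | 80%/80% apparently met | 80%/80% truly met |
|---|---|---|---|
| 0.3 | +4.6/+1.7 | 69% of runs | 37% of runs |
| 0.6 | +5.4/+1.9 | 21% of runs | 0% of runs |

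**The case against.** The strongest reply is that much of the study is sound external validation, and that the stated aim attaches a cut-off only to pyuria: it speaks of biomarkers, but of a cut-off value for pyuria. Future implications also describes a development aim, for which deriving thresholds is legitimate. This stands in part. A reader might infer that nothing is validated, and that would be wrong: pyuria is tested at a value fixed from the pilot, and the AUCs check each marker's discrimination in new patients without any search. What remains is that accuracy at a threshold is also to be reported for each biomarker, and that part is derived, not validated.

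Three further inferences are tempting, and the documents do not support them.

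- **That the planned precision collapses.** For the 76%/72% marker, the SD of reported sensitivity is about 8.3 points, against a binomial √(0.76 × 0.24 / 70) = 5.1. But the true sensitivity at the chosen cut-off itself varies with an SD of about 8.0, because the cut-off moves along the curve. The error, reported minus true, has an SD of only about 4.9. The main fault is an interval centred too high, not one far too narrow. Part of the Wald shortfall belongs to that interval type near 90%.
- **That subgroup results carry a much larger bias.** The plan says performance will be assessed in subgroups. It does not say that cut-offs will be searched again there, and it gives no subgroup sizes.
- **That a comparison with pyuria is tilted.** No formal comparison of biomarkers with pyuria is planned. Only an informal side-by-side reading would be affected.

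It is also fair that the article gives no pilot biomarker cut-off, and that the pilot enrolled older women only, whereas this study includes men and several settings. Whether those cut-offs transfer cannot be judged from the document. An optimism correction might sit in a fuller plan that is not shown. Even so, the stated rule would remain a re-derived cut-off.

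**Conclusion.** The point holds for the biomarker cut-offs and the combination, and only for them. As written, their sensitivity, specificity, predictive values and likelihood ratios will be optimistic on average, and no biomarker cut-off or panel rule will have been validated.

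The size is modest for single markers: at most about 4 of the 10 points of planned precision, at the weakest corner of the pilot range. It is an average. In a single dataset the error can go the other way: apparent sensitivity fell below the true value in about 20% of simulated studies, and specificity in about 35%. The panel is at least as exposed, and a pass on its 80%/80% target cannot be taken at face value.

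The figures rest on an equal-variance binormal marker, the Youden index, 30% prevalence with 234 analysed patients and, for the panel, assumed correlations. Another definition of optimal would change the numbers. The same-sample selection would remain.

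**What to change.** 1. Where the pilot cut-off and assay scale carry over, lock each biomarker's pilot cut-off, and the pilot panel rule, before the data are analysed. Report their accuracy here as the validation result.
2. Label newly derived cut-offs and the refitted combination as exploratory. Make them primary only for a marker or panel with no pilot rule that carries over, and say so in advance.
3. Define optimal. Report any derived cut-off or refitted panel with a bootstrap or cross-validation optimism correction that repeats both the cut-off search and the model fit in each resample, and take confidence intervals from the same procedure. Judge the 80%/80% target on the corrected values.
4. In subgroups, apply the same overall cut-off and do not search for a new one.

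The AUC analysis and the pyuria analysis can stay as they are. The cost is some wording in the analysis plan, a check that pilot and current assay scales match, and a resampling script. No new patients or samples are needed. The downside is slightly less favourable accuracy figures.

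### The biomarker panel is fitted and, as written, scored in the same roughly 70 UTI cases, with no correction described, so its accuracy against the 80%/80% aim will look too good

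*Protocol article*

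**What the plan says.** The Outcome measures section lists a biomarker combination among the primary outcomes, beside the five single markers and pyuria at 200 leukocytes/µL. The Introduction and Discussion describe the study's purpose as validation.

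The Analysis of outcome measures section gives the panel one sentence: a logistic regression is run "to assess the value of combination(s) of biomarkers, aiming at a minimal sensitivity and specificity of 80" per cent. For each single marker, the same section takes the optimal cut-off from the study's own ROC curve and reports the accuracy at that cut-off. Only pyuria has a threshold carried over from the pilot.

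A panel with known performance already exists. The Sample size section reports: "For the biomarker panel, specificity was 91% at a sensitivity of 88" per cent. The article does not give that panel's markers, coefficients or cut-off, and does not say that it will be applied unchanged. The Future implications section adds that the study is meant to identify the most suitable marker signature for a point-of-care test.

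The sample size rests on single markers, chosen "to have an adequate sample size for assessment of both the individual markers and the panel".

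**The concern.** Validation means applying a rule fixed beforehand to new patients. Estimating coefficients and a cut-off in the study data, and then reading sensitivity and specificity from the same patients, is model development. The figures it gives are optimistic because the model has partly fitted chance features of the sample. Choosing among several combinations adds to the optimism.

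A numerical aim makes this matter more, since a panel truly below 80%/80% can appear to reach it. The panel result is also a primary outcome and may inform which markers go into a point-of-care test. Overstated sensitivity would mean more missed infections than the report suggests.

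**Working it through.** **Inputs from the Sample size section.** The half-width comes from "maximum marginal error of estimate of 0.10 (δ) for constructing CI of true value of specificity" at the 95% level. Prevalence is 30%. The assumed single-marker values are 72% specificity and 76% sensitivity. The pilot panel had 88% sensitivity and 91% specificity.

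**The plan's own figures.** n = 1.96² × p(1−p) / 0.10², divided by the share of patients who are non-diseased or diseased.
- Specificity: 77.4 / 0.70 = 110.6 (stated 110).
- Sensitivity: 70.07 / 0.30 = 233.6, rounded to 234 (stated 234).
- Drop-out: 234 × 1.05 = 245.7, rounded to 246 (stated 246).

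The figures reproduce. They imply 234 × 0.30 = 70 UTI cases and 164 non-cases.

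**Precision for a fixed panel.** At 88% sensitivity with 70 cases: 1.96 × √(0.88 × 0.12 / 70) = 0.076. This is inside the ±0.10 criterion.

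**Assumptions for the simulation (not in the documents).** Five equally informative normal markers with common correlation 0.5, and a cut-off maximising the smaller of sensitivity and specificity. Five markers give 10 + 10 + 5 + 1 = 26 combinations of two or more.

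**Scenario just below the aim: best attainable panel 77%/77%.**

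| Analysis | Chance of an apparent 80%/80% |
|---|---|
| Rule locked in advance | about 6% |
| Full five-marker model, fitted and scored in-sample | about 26% |
| Best of 26 combinations, fitted and scored in-sample | about 39% |

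The locked figure is exact binomial: P(at least 56 of 70) × P(at least 132 of 164) = 0.332 × 0.167 = 0.055. In no simulated trial did the fitted panel truly meet 80%/80%.

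**Sensitivity to the assumptions.** With a best attainable panel of 78%/78% and correlation 0.3 to 0.7, the rates are 35–39% (full model) and 53–58% (selected). At 76%/76% they are 15–18% and 25–32%.

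**Does a correction work?** At correlation 0.5, 10-fold cross-validation repeating selection, fitting and cut-off choice cuts the selected-panel rate from 58% to about 10% (78%/78%) and from 25% to 3% (76%/76%). At 78%/78% its mean estimate was 74.9%/78.1%, against a true 74.8%/77.8%.

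**Scenario near the pilot: best attainable panel 89.5%/89.5%.** The apparent result met 80%/80% in every replicate, and the true result did in 98–99%. Mean apparent against true sensitivity:
- Full model: 90.3% against 87.6%, a difference of 2.7 points.
- Selected combination: 91.2% against 86.5%, a difference of 4.7 points.

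**The case against.** **It may only be missing detail.** This is a condensed article, and an unseen analysis plan could hold an optimism correction. The optimal-cut-off rule is written for single markers, and extending it to the panel is the natural reading but is not stated. This lowers the weight of the point but does not remove it. The article does fix a method (a new regression in the study data) and an accuracy aim, and that method does not match the stated purpose of validation.

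**The 77%/77% scenario sits just under the aim.** This is true. With correlation 0.5 it implies about 72%/72% per marker, below the pilot's lowest sensitivity (76%) and at its lowest specificity (72%). Giving every marker the worst pilot pair yields a best panel of about 80% at correlation 0.5, 83% at 0.3 and 77% at 0.7. The scenario therefore shows what can happen and is not a forecast. Lower performance than in the pilot cannot be excluded, because that cohort was older women and this study adds men and several care settings.

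**Stronger readings that the article does not support.**
- A reader might infer an exhaustive subset search. The article speaks only of assessing combinations; selection is an inference from that wording and from the aim of identifying a signature.
- A reader might infer a go/no-go rule judged on the point estimate. The article states an aim, does not say how it will be judged, and foresees further test development and an impact study.
- A reader might infer that the sample size is too small for the panel. The calculation concerns precision, a fixed panel meets it, and no test against 80% is claimed.

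**Conclusion.** The point holds in a limited form. As written, the primary panel analysis yields in-sample accuracy under the name of validation. The optimism is about 3 points of sensitivity for a single full model and about 5 for a selected combination when true performance is near the pilot's. There the 80%/80% conclusion is safe and only the reported figure is inflated. When true performance is a few points below 80%, the chance of appearing to meet the aim is roughly four to seven times that of a locked rule at 77%/77% (26% or 39% against 5.5%). These sizes depend on the assumed normal, equally informative markers, the assumed correlation and the cut-off rule. The direction of the bias does not depend on those particular choices.

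**What to change.** In the Analysis of outcome measures section:

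1. Name one panel model in advance, for example all five markers.
2. Report bootstrap- or cross-validation-corrected sensitivity and specificity with 95% confidence intervals, repeating any marker selection and cut-off choice within each resample.
3. Compare the 80%/80% aim with the corrected estimate and its interval. For scale, an observed 80% in 70 cases has a half-width of 1.96 × √(0.80 × 0.20 / 70) = 9.4 points.
4. Where the pilot panel's coefficients and cut-off are available and the assays are comparable, also report that panel applied unchanged, as the direct external validation. Whether it should be the primary panel analysis is debatable, given the broader population.

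The cost is a resampling script, a few lines of text and a slightly less favourable panel figure. The sample size need not change. The model should be named before biomarker results are linked to UTI status, because it cannot credibly be pre-specified afterwards.
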